### Plans to give access to the full protocol, participant-level data, and statistical code {31c}

The full protocol, participant-level data, and statistical code will not be made publicly available during the course of the study. However, after the study is completed and the results are published in a peer-reviewed journal, these materials will be available upon request. This ensures transparency and reproducibility while maintaining participant confidentiality. Access will be granted to authorized researchers or institutions, with any personally identifiable information removed to protect privacy.

## Oversight and monitoring

### Composition of the coordinating centre and trial steering committee {5d}

The trial will be overseen by the supervising professor and the advisory committee, who will monitor the progress of the study and ensure that all aspects of the study are conducted according to the protocol. The supervising professor is responsible for providing high-level guidance, while the advisory committee will offer additional support and advice on specific areas of the study.

Any issues or concerns arising during the trial will be addressed by the supervising professor and advisory committee, who will make decisions regarding the study’s progress. Ethical approval for the study has been granted by the university’s ethics committee, ensuring the study meets all ethical standards.

### Composition of the data monitoring committee, its role and reporting structure {21a}

This study does not have a Data Monitoring Committee (DMC) due to its educational and low-risk nature. The study is not expected to involve significant risks or adverse events that would require ongoing oversight by an independent committee.

However, the progress of the study and the integrity of the data will be monitored by the supervising professor and the advisory committee, who will ensure that the study follows the protocol and ethical guidelines. Any concerns or issues arising during the study will be addressed by these individuals, who will make decisions about the continuation of the study.

### Adverse event reporting and harms {22}

In this study, participants will be closely monitored for any adverse events or unintended effects resulting from the intervention. Participants will be encouraged to report any negative effects they experience during the trial, and routine assessments will be conducted at each follow-up session to identify any potential adverse events.

All reported adverse events, whether solicited or spontaneously reported by participants, will be documented and assessed for severity. If an adverse event occurs, the research team will evaluate whether it is related to the intervention and determine the necessary course of action, including whether the participant should continue in the study or whether the intervention needs to be modified.

Adverse events will be reported to the university’s ethics committee and any relevant regulatory bodies, as required. The research team will take appropriate steps to manage and address any adverse effects, ensuring the safety and well-being of all participants.

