### Intervention description {11a}

After obtaining approval from the School of Nursing and Midwifery, Isfahan University of Medical Sciences, and presenting it to the officials of the Parkinson’s Charity Association, the researcher will enter the study setting and select participants based on inclusion criteria and neurologist confirmation. After obtaining written informed consent, participants will complete baseline questionnaires (demographic and clinical information form, PFS-16, GSE-17, and PDQ-8) in a 30–45-min session.

Participants will then be randomly assigned to either the intervention group (*n* = 40) or the control group (*n* = 40) using block randomization. After completing consent forms and baseline assessments, the CCM—comprising four stages: familiarization, sensitization, control, and evaluation—will be implemented for the intervention group over a period of 8 weeks (2 months).

The control group will receive no intervention and will continue with standard medical treatment and routine care as prescribed by their physician [40].

In the first phase of the CCM, known as the familiarization stage, the study participants in the intervention group (including the patient and their caregiver) attend a session lasting approximately 30 to 45 min. This session takes place in a quiet room with appropriate lighting and temperature, free from environmental distractions, within the Parkinson’s Association.

During this stage, the nurse is introduced to the patient and their caregiver, and the expectations of the nurse at different stages of the study are outlined. Additionally, the expectations and needs of the patient and caregiver are identified. Recommendations are provided regarding the importance of continuity in the caregiving relationship and minimizing interruptions until the designated period ends. Moreover, the schedule for in-person and telephone follow-ups is established, and the objectives and means of communication, along with the structure of educational sessions, are explained [40].

The second phase of the CCM, known as the sensitization stage, aims to enhance the awareness of patients and their families regarding the nature of the disease, its early and late complications, preventive measures, and associated limitations. This stage actively involves both the patient and their family in addressing the chronic condition and encourages the adoption of appropriate health behaviors.

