During the sensitization stage, participants in the intervention group will attend weekly sessions for four consecutive weeks (a total of four sessions), with each session lasting approximately 30 to 45 min. These sessions will take place in a quiet room with appropriate lighting and temperature, free from environmental distractions, within the Parkinson’s Association. To improve the effectiveness of the training, educational slides and pre-recorded videos on PD will be used.

The key activities in this phase primarily involve care counseling, which will be conducted in group sessions. The main topics covered in these follow-up care sessions (as outlined in Table 1) include an explanation of PD and its symptoms in a way that is comprehensible to patients and their families, the acute and chronic complications of the disease and their management, the importance and implementation of a proper diet and physical activity, and the significance of adhering to prescribed medications. Together, the first and second phases constitute the initial month of the intervention program [40].

**Table 1 Tab1:** Content of the sessions conducted for the intervention group

Stage	Educational behavioral objectives	Content	Teaching method	Presenter	Duration
First stage: the familiarization stage	• Learners should express their expectations regarding CCM sessions • Scheduling in-person meetings in consultation with patients and their companions • Gathering feedback from learners on the objectives of CCM sessions	• Introducing the nurse to the patient and their companion, clarifying the nurse’s expectations at different stages of the study • Identifying and addressing the expectations and concerns of the patient and their companion • Providing recommendations on the necessity of continuity in the care relationship, emphasizing minimal disruption until the designated period ends • Establishing and agreeing on schedules for in-person and phone meetings, outlining the objectives and methods of communication and educational sessions	• Lecture • Q&A (Question and Answer) • Group Discussion	Researcher	30 to 45 min

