Ninth stage: control phase	• Learners are expected to have sufficient knowledge of previous sessions and actively express their understanding during the review of past topics • Learners should articulate any questions or challenges they face and implement the solutions provided by the researcher • Learners should actively describe the health behaviors they have adopted since the completion of the sensitization sessions	• Continuation of continuous Care Consultations to Sustain Health Behaviors Based on Patients’ Needs and Challenges • Encouraging Patients to Maintain Healthy Behaviors	• Phone Call and Q&A	Researcher	30 to 45 min
Tenth stage: evaluation phase	• Completion of Questionnaires by Participants • Learners should express any new or unresolved issues and listen to the solutions provided by the researcher or the experiences of other participants regarding the existing problem	• Review of the Care Process, Evaluation of Key Indicators through Recompletion of Questionnaires, and Monitoring and Controlling Patient Behavior and the Impact of Provided Training • Assessment of Unresolved Issues or the Emergence of New Problems	• Lecture • Q&A • Group Discussion	Researcher	30 to 45 min

In the monitoring phase, follow-up care counseling continues to reinforce the maintenance of healthy behaviors. This phase is carried out over 4 weeks through four telephone calls (one call per week) with the patient and, if necessary, with their caregiver. The content of these calls is tailored to the patient's specific problems and needs.

A key component of this phase is encouraging the patient to sustain healthy behaviors and referring them to a specialist if required. Additionally, a contact number will be provided to patients and their caregivers, allowing them to reach out with any questions and receive necessary guidance [40].

The evaluation phase, which is the final step of the intervention, involves assessing the care process, evaluating key indicators through the reassessment of questionnaires, and monitoring the patient’s behavior to determine the impact of the provided education. Additionally, any unresolved issues or newly emerging problems will be examined [40].

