## Discussion

Based on previous studies, various methods have been implemented to manage fatigue, enhance self-efficacy, and improve the QOL in patients with PD. However, each approach has faced challenges, one of which is the lack of a comprehensive strategy to address these variables effectively.

The Ahmadi CCM primarily focuses on caring for individuals with chronic diseases who require ongoing supervision and support. One of the core principles of this model is patient and family education and empowerment. Patients learn how to manage their condition and actively participate in their own treatment and self-care. The educational components of this model cover medication management, lifestyle modifications, and healthy nutrition.

Another key principle of this model is supporting patient self-care. Patients are encouraged to take greater responsibility for their health and well-being. Additionally, continuous monitoring and follow-up play a crucial role in the Ahmadi model. Regular follow-up sessions and ongoing communication—either in person or via telephone—are conducted to assess the patient’s health status.

Overall, this model provides a comprehensive and proactive approach to chronic disease management, placing the patient at the center of the care process and enabling them to play an active role in maintaining and improving their health.

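### Adverse-event enquiry is tied to an undefined follow-up session, so harms counts by arm would probably rest on unequal ascertainment

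*Protocol article*

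**What the plan says.** Protocol article, *Adverse event reporting and harms {22}*: events are collected in two ways. They are solicited ("routine assessments will be conducted at each follow-up session to identify any potential adverse events") and they are volunteered ("Participants will be encouraged to report any negative effects they experience during the trial"). Both kinds are documented, and the section does not say that they will be kept apart. It neither defines a follow-up session nor gives a separate enquiry schedule for controls.

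*Intervention description {11a}* sets out the intervention arm's contacts:
- one familiarization meeting, at which patient and caregiver "attend a session lasting approximately 30 to 45 min";
- sensitization, with "weekly sessions for four consecutive weeks (a total of four sessions";
- a control phase with "four telephone calls (one call per week";
- a closing evaluation session at which the questionnaires are completed again.

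That arm is also given a telephone number for questions. For the other arm the same section says: "The control group will receive no intervention and will continue with standard medical treatment and routine care as prescribed by their physician".

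*Outcomes {12}* places two post-baseline questionnaire assessments in both arms, one just after the programme and one a month later.

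**The concern.** If one arm is asked about harms more often than the other, recorded events can differ when true event rates do not. The *Introduction* lists postural instability among the features of Parkinson's disease, so falls and similar background events are to be expected in both arms. The last sensitization session in Table 1 covers physical activity, walking aids, balance and home safety. The programme could therefore plausibly shift such events in either direction, and the control arm is the only concurrent reference for judging this.

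With unequal enquiry, an excess in the intervention arm could not be told apart from more frequent asking, and a real excess could be dismissed as an artefact. The protocol regards the intervention as free of direct risk and has no data monitoring committee. Harms data gathered on an unequal basis would be weak support for that view.

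**Working it through.** The plan states no number of adverse-event enquiries per arm, so there is no figure to reproduce. The check has three parts: what the term means in this article, how many contacts each reading gives, and what an unequal number of contacts could do.

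**Meaning of the term.**
- *Intervention description {11a}*, on the four sensitization sessions: "The main topics covered in these follow-up care sessions". The same section speaks of in-person and telephone follow-ups agreed at familiarization, and of follow-up counselling in the weekly calls.
- *Discussion*, on the components of the care model: "Regular follow-up sessions and ongoing communication", in person or by telephone.
- *Outcomes {12}* and *Trial design {8}* describe the questionnaire time points as assessments and do not call them follow-up sessions.

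The article's own usage therefore points to care-model contacts. That is an inference, because {22} itself is silent.

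**Counts per participant after baseline.** The evaluation session is also the immediate post-intervention assessment in the intervention arm, so it is counted once.

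| Reading of follow-up session | Intervention | Control |
|---|---|---|
| Programme contacts only | 1 + 4 + 4 + 1 = 10 | 0 |
| Programme contacts and both shared assessments | 10 + 1 = 11 | 2 |
| As above, without the familiarization meeting | 11 − 1 = 10 | 2 |
| Sensitization sessions and both shared assessments | 4 + 2 = 6 | 2 |
| The two shared assessments only | 2 | 2 |

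With 10 or 11 contacts against 2, the ratio is 10/2 = 5 to 11/2 = 5.5. Over 40 participants per arm that is 40 × 10 = 400 to 40 × 11 = 440 contacts, against 40 × 2 = 80.

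**What unequal contact could do.** This is an illustration only. Assume that each contact has the same independent chance p of producing an adverse-event record in both arms, with no true difference. The chance of at least one record over k contacts is 1 − (1 − p)^k.

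| Assumed p | k = 11 | k = 2 |
|---|---|---|
| 0.02 | 1 − 0.98^11 = 19.9% | 1 − 0.98^2 = 4.0% |
| 0.05 | 1 − 0.95^11 = 43.1% | 1 − 0.95^2 = 9.8% |
| 0.10 | 1 − 0.90^11 = 68.6% | 1 − 0.90^2 = 19.0% |
| 0.20 | 1 − 0.80^11 = 91.4% | 1 − 0.80^2 = 36.0% |

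No value of p comes from the document. The model also ignores that an enquiry after a longer gap covers more time. With perfect recall at the two shared assessments, 11 versus 2 enquiries would yield the same events. The more is forgotten between enquiries, the larger the distortion. The table shows the direction of the bias and does not estimate its size.

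**The charitable reading.** At 2 versus 2, solicited events are on an equal footing. Volunteered events are not: the intervention arm speaks with the researcher about weekly during the programme and holds a contact number. Because {22} does not separate the two sources, the combined record still favours recording in that arm.

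**The case against.** The strongest reply is that {22} does not state an asymmetry. The term is undefined, and a reader may take it to mean the two assessments that both arms attend. Counting all 11 contacts stretches it: the familiarization meeting is a first contact and hardly a follow-up. This stands. The figure of 11 versus 2 is an upper count on one reading and not something the protocol fixes.

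A reader might go further and infer that harms cannot be compared between the arms at all. The documents do not support that. Events solicited at the two shared assessments would be comparable, and volunteering is open to participants in either arm. The difficulty lies in the pooled record.

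A reader might also infer that a planned analysis is biased. None is planned: harms are not a listed outcome, and *Statistical methods {20a}* covers only the three questionnaire scores. Section {22} is mainly about handling individual cases, and for that purpose asking more often where the exposure occurs is reasonable. But counts by arm in a randomised trial will be read as a comparison whether or not a test is attached.

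Nor does {22} promise controls the same close monitoring. Its wording concerns unwanted effects of the intervention. Open-label judgement of relatedness follows from the declared design and is not a separate defect.

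Other contacts might narrow the gap, but their arm and number are not given. *Participant retention {18b}* mentions calls to support adherence, and *Post-trial care {30}* mentions three further months of follow-up. Neither can be counted on to restore balance.

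Finally, question sets and visit forms may well be in a fuller protocol. That is fair as to detail. The point here concerns the enquiry rule that the article does state.

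**Conclusion.** The point holds in limited form. Section {22} ties solicited enquiry to a term that the article otherwise uses for contacts only the intervention arm receives. On that best-supported reading there are up to 10 programme contacts, or 11 with the one-month assessment, against at most 2 for controls. On the charitable reading solicitation is 2 versus 2 and only the opportunity to volunteer events is unequal. Either way, counts by arm from the pooled record would be expected to lean towards more events in the intervention arm, given that recall is imperfect. The size of the bias cannot be derived from the document.

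A reader might also infer that unequal detection would drive unequal dropout and so distort the quality-of-life result. The document gives no figures from which to establish that, and it is not claimed here. This is a cheap improvement to harms reporting.

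**What to change.** In {22}:
1. State that adverse events are solicited with the same short fixed question set in both arms at the immediate post-intervention and one-month assessments, and that only these events are used for any between-arm harms statement. Solicited enquiry then becomes 2 versus 2 per participant, or 40 × 2 = 80 in each arm if all are assessed.
2. Record the source of every event found or volunteered at CCM sessions, on calls or through the contact number. Report these separately, as a description of the intervention arm.
3. Report the number assessed per arm. *Exclusion criteria* and *Participant retention {18b}* remove excluded or discontinued participants from follow-up, so the questions would not reach everyone randomised. Alternatively, reconcile those sections with {22} so that the harms questions are also asked of participants who stop.

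The cost is a slightly longer questionnaire at two assessments that already take place, with no extra visits. Following those who stop, if chosen, would also require amending the two sections named.

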### Frequency and plans for auditing trial conduct {23}

In this study, the oversight and monitoring of the trial will be carried out by the supervising professor and advisory committee. They will continuously review the progress of the study and ensure that it is conducted according to the protocol and ethical guidelines. Additionally, the university’s ethics committee may perform random oversight or additional monitoring if necessary.

### Plans for communicating important protocol amendments to relevant parties (e.g., trial participants, ethical committees) {25}

In accordance with the SPIRIT guidelines, the following plans outline how important protocol amendments will be communicated to relevant parties involved in the trial, such as trial participants, ethical committees (REC/IRB), investigators, trial registries, journals, and regulators.Trial Participants: If there are any amendments that impact the eligibility criteria, outcomes, or the overall intervention, trial participants will be informed promptly and clearly. Communication will be through written notifications, and if necessary, verbal communication will be arranged by the study team. Participants will also be provided with updated consent forms if the protocol changes affect their participation.Ethical Committees (REC/IRB): All significant protocol modifications, particularly those that may affect participant safety, eligibility, or the scientific integrity of the study, will be submitted to the relevant Ethics Committees (REC/IRB) for review and approval. Any changes that are deemed necessary by the REC/IRB will be addressed before implementation.Investigators and Trial Staff: All investigators and trial staff will be immediately informed of the amendments through official correspondence. Training sessions or briefings will be organized if necessary to ensure that everyone involved is fully aware of the changes and their implications for trial conduct.Trial Registries: The protocol amendments will be updated in the relevant trial registries to ensure that public records of the trial reflect the most accurate and up-to-date information.Journals and Publications: If the trial has already been published or if there are plans for publication, any relevant amendments will be communicated to the journals in order to update previously submitted or published protocols and results.Regulators: If the protocol amendments are substantial, especially in terms of safety or scientific aspects, the relevant regulatory bodies (e.g., FDA, EMA) will be notified in accordance with regulatory requirements. The necessary documentation will be submitted to ensure compliance with regulatory standards.

By following these communication plans, we aim to ensure transparency, maintain the integrity of the trial, and ensure that all parties are kept informed of the protocol amendments in a timely and efficient manner.

### Dissemination plans {31a}

The results of this clinical trial will be submitted for publication in reputable peer-reviewed scientific journals. In addition, a summary of the findings will be shared with trial participants in a clear and understandable format. Healthcare professionals and other relevant stakeholders will be informed through professional networks and scientific communications. Primary outcome data and other relevant datasets will be made publicly available through trial result registries or open-access repositories, where applicable. There are no publication restrictions imposed by the sponsor or any other party.

